### Blood pressure monitoring

An automatic BP cuff on the unaffected arm (right arm is chosen when both sides are affected or unaffected) is used to monitor the BP (SBP, diastolic BP, and mean arterial pressure). During the first 24 h after randomization, BP is recorded every 2 h. On days 2 and 3, BP is recorded every 4 h. During days 4–7, BP is recorded every 8 h. On the day of hospital discharge, BP at 08:00 is recorded. Three measurements of BP are required for each time point and the average is recorded.

### Data quality

The following procedures to minimize bias and ensure data quality and protocol standardization are required: (1) a training session will be held for research coordinators from all the participating centers before the commencement of CHASE study; (2) the principal investigator in each research site takes charge of quality control by supervising the conduct of the trial in accordance with the prespecified protocol, applicable guidelines, and regulations; (3) all participating sites will have monitoring visits via video conferencing after every ten patients are randomized, to verify consent, eligibility criteria, anomalous data, and reported serious AEs; (4) the Shaanxi Cerebrovascular Disease Clinical Research Center (SCRC) will prepare monthly reports on recruitment, randomization, data completeness, and protocol adherence. Case report forms and informed consent forms will be securely stored in a locked cabinet in a secure office with limited access. All digital data will be password-protected and stored in a firewall-protected secure environment. The trial sponsor has access to the final trial dataset.

### Outcome measurement

The primary outcome measurement is the proportion of participants with a poor outcome at day 90 of enrollment. Poor outcome is defined as major disability (mRS ≥ 3, unable to live independently) or all-cause death. The proportion of participants with a poor outcome at hospital discharge is the key secondary outcome. Other secondary outcomes are the disability (evaluated by NIHSS, GCS, and Barthel index) at hospital discharge and the ability of activities of daily living at day 90 of enrollment evaluated by Barthel index. Outcomes are assessed independently by trained research assistants who are blind to the grouping results and clinical data. The 90-day outcomes are evaluated via telephone interviews at day 90 of enrollment (a delay of up to three days is acceptable). In cases when the patient is incapable to complete the interview, the first choice for a proxy is the spouse/live-in companion.

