**Methods/design:**

The CHASE trial is a multicenter, randomized, controlled study. A total of 500 adult patients with acute severe stroke will be enrolled in 18 study sites in China and randomized to individualized BP lowering (10–15% reduction from admission level) or guideline-recommended BP lowering. The primary outcome measurement is the proportion of participants with a poor outcome (modified Rankin Scale ≥ 3) at day 90 of enrollment. Secondary outcomes include disability at hospital discharge and the ability of activities of daily living at day 90 of enrollment. The relationship between intervention and the primary outcome will be analyzed using multivariate logistic regression adjusted for study site, demographics, and baseline characteristics.

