### Study procedures

Table 2 presents all the variables measured at each time point of the study. At the time point of baseline screening, demographics, subtypes of stroke, medical history (e.g. AIS, ICH, coronary event, diabetes mellitus, and hypertension), physical examination, clinical scores (NIHSS, GCS, Barthel index, mRS), and vital signs are recorded. On day 1 and day 7, routine laboratory tests for stroke patients are assessed, including blood routine, liver and renal function test, serum lipid, fasting glucose, urine routine, and electrocardiography. Co-morbidities on the day of screening and hospital discharge are recorded. Clinical scores on day 7, the day of hospital discharge, and day 90 are collected. During the whole hospitalization, BP, vital signs, and adverse events (AEs) are monitored, and concomitant treatments are documented.

**Table 2 Tab2:** Timing and content of study assessments

Items	Day of enrollment									
	Screening	1	2	3	4	5	6	7	HD	90
Written informed consent	●									
Inclusion and exclusion criteria	●									
Demographics	●									
Medical history	●									
Physical examination	●							●	●	
BP monitoring	●	●	●	●	●	●	●	●	●	
Laboratory tests		●						●		
NIHSS and GCS	●								●	
Barthel index and mRS	●								●	●
Vital signs monitoring	●	●	●	●	●	●	●	●	●	
Co-morbidities	●								●	
AEs		●	●	●	●	●	●	●	●	
Use of antihypertensive agents		●	●	●	●	●	●	●	●	
Concomitant therapies		●	●	●	●	●	●	●	●	

*HD* hospital discharge, *BP* blood pressure, *GCS* Glasgow Coma Scale, *NIHSS* National Institute of Health stroke scale, *mRS* modified Rankin Scale, *AE* adverse event

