### Statistical and analytical plan

Patients will be analyzed according to the intention-to-treat principle. Analyses will be conducted at the Shaanxi Cerebrovascular Disease Clinical Research Center by blinded biostatisticians. Baseline characteristics will be summarized using univariate analyses. Categorical variables will be presented as the number and percent, whereas the continuous variables will be presented as mean (± standard deviation) or median (interquartile range). We will compare the proportions for the primary and secondary outcomes between patients randomized to the individualized BP-lowering group vs the guideline-recommended BP-lowering group using the Chi-square test. We will calculate the relative risk reduction, absolute risk reduction, and the number needed to treat with individualized BP-lowering target to prevent one death. Logistic multivariate analyses will be used to adjust for potential confounding effects of different variables and estimate adjusted odds ratios and associated 95% confidential intervals. Two-sided *p* values ≤ 0.05 will be considered significant. Statistical analysis will be performed with SPSS version 22 software (SPSS Inc., Chicago, IL, USA).

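### No stated analysis commits to using the screening NIHSS or GCS when the same scale is compared at discharge, so two secondary comparisons may give up precision the trial already holds

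*Protocol article*

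**What the plan says.** Outcome measurement lists, after the primary and the key secondary outcome: "Other secondary outcomes are the disability (evaluated by NIHSS, GCS, and Barthel index) at hospital discharge".

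Under Study procedures, at baseline screening, "clinical scores (NIHSS, GCS, Barthel index, mRS), and vital signs are recorded". Later, "Clinical scores on day 7, the day of hospital discharge, and day 90 are collected". Table 2 marks NIHSS and GCS at screening and at hospital discharge, so text and table agree on the two time points that matter here.

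The Statistical and analytical plan says: "We will compare the proportions for the primary and secondary outcomes between patients randomized to the individualized BP-lowering group", against the "guideline-recommended BP-lowering group using the Chi-square test". It then adds: "Logistic multivariate analyses will be used to adjust for potential confounding effects of different variables". That sentence names neither the outcomes nor the variables.

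The abstract, under Methods/design, is more specific, but about one outcome: "The relationship between intervention and the primary outcome will be analyzed using multivariate logistic regression adjusted for study site, demographics, and baseline characteristics".

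**The concern.** A patient's neurological score at admission usually predicts the same score at discharge. If it does here, a comparison of arms at discharge that ignores the screening value leaves explainable variation in the error term. The interval is then wider, and a real short-term effect on neurological deficit is easier to miss. The data needed to avoid this are already collected.

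This is a separate matter from whether a chi-square test suits an ordinal score, and from how deaths are scored. Replacing the chi-square test with an unadjusted rank test that ranks deaths worst would still leave the screening value unused.

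**Working it through.** **What the text commits to.** Taking the stated analyses in turn for discharge NIHSS and GCS:

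- *Chi-square test of proportions.* It is applied expressly to the secondary outcomes and uses no baseline information. No cut-point that would turn NIHSS or GCS into a proportion is given.
- *Logistic models in the analysis section.* They are not restricted to the primary outcome and do not rule out screening NIHSS or GCS as covariates. They do not commit to either. For a score they would give odds ratios only after a split at a cut-point that is not stated.
- *Logistic model in the abstract.* It includes baseline characteristics but is described for the primary outcome.

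None of the three commits to using the scale's own screening value.

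**Figure to reproduce.** The article gives no power or precision figure for these scales. Its sample size of 500 is for the primary outcome, and this point does not rest on it.

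**Inputs.**
- From the article: 500 patients, 1:1 allocation, 5% overall loss, two-sided 5% test. This gives 500 × 0.95 = 475 analysed, or 237.5 per arm. Applying the 5% to a discharge score is an assumption; the variance ratios below do not depend on it.
- Assumed: the screening-to-discharge correlation r, shown from 0.2 to 0.7. Results are in units of the discharge SD, so no SD has to be assumed.

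**Formulas (linear model adjusted for the screening score).**
- Residual variance ratio = 1 − r²
- Interval width ratio = √(1 − r²)
- Unadjusted 95% half-width = 1.96 × √(2/237.5) = 0.180 SD
- Equivalent sample size = 475 / (1 − r²)
- Benchmark effect with 80% unadjusted power: (1.960 + 0.842) × √(2/237.5) = 0.257 SD
- Adjusted power at that effect = Φ(2.802/√(1 − r²) − 1.960)

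| r | Variance removed | Width ratio | Half-width (SD) | Equivalent N | Power at 0.257 SD |
|---|---|---|---|---|---|
| 0 | 0% | 1.000 | 0.180 | 475 | 80% |
| 0.2 | 4% | 0.980 | 0.176 | 495 | 82% |
| 0.3 | 9% | 0.954 | 0.172 | 522 | 84% |
| 0.4 | 16% | 0.917 | 0.165 | 565 | 86% |
| 0.5 | 25% | 0.866 | 0.156 | 633 | 90% |
| 0.6 | 36% | 0.800 | 0.144 | 742 | 94% |
| 0.7 | 49% | 0.714 | 0.128 | 931 | 97.5% |

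**Reach of the table.** The r = 0 row is an unadjusted comparison of mean scores, not the chi-square test in the article. Splitting a normal score at the median and using chi-square would give about 61% power at the same 0.257 SD. That further loss comes from dichotomising and is not counted here. The table also treats all 475 patients as having a numeric score.

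**The case against.** **This is a condensed article, and covariate lists for lower-tier outcomes usually sit in a fuller plan.** That is fair, and silence alone would be no finding. But the article is not silent. It names a test and applies it to the secondary outcomes, so the point concerns a stated method. The fuller plan may already contain the adjustment, in which case the article's wording only needs to be brought into line.

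**The logistic sentence may already cover it.** A reader might infer that discharge NIHSS and GCS will be compared only by an unadjusted test. The text does not support that: the adjustment sentence is general, and the abstract describes the primary analysis without saying that adjustment stops there. What stands is narrower, namely that nothing commits to each scale's own screening value.

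**The gain may be small.** This stands. Entry at GCS of 12 or less, or NIHSS of 11 or more, trims the mild end, and the day of discharge varies; both may lower r. Against that, the two criteria are joined by ‘or’ and neither scale is capped at the severe end, so some spread remains. The document cannot settle it, and quoting only r of 0.5 to 0.7 would be favourable to the criticism.

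**Linear results do not carry over directly to an ordinal or rank model.** This also stands. In a proportional-odds model, adjustment mainly shifts the odds ratio and raises power; it does not narrow the interval as linear adjustment does. Deaths placed in the worst category may also weaken the link with the screening score.

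**Validity is untouched.** Agreed. With 1:1 randomization, the unadjusted comparison is unbiased on average and its standard error already allows for chance imbalance in severity. A reader might infer a biased result or an inflated type I error; neither follows.

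**Conclusion.** The point holds as a modest one about efficiency. For discharge NIHSS and GCS, the only between-arm test specified is unadjusted, and the added logistic models do not commit to the screening value of the same scale, although it is collected. Under a linear model the variance that adjustment could remove is about 4% at r = 0.2, 9% at 0.3, 25% at 0.5 and 49% at 0.7. The correlation is an assumption throughout, so the size of the benefit is uncertain; its direction is not in doubt for any appreciable r. In the ordinal or rank model proposed, the benefit should be read as power and need not match these figures. The primary outcome and the key secondary outcome are not affected.

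**What to change.** In the Statistical and analytical plan, state that discharge NIHSS and discharge GCS are each compared as scores by a proportional-odds or rank-based covariance model. The model contains arm and that scale's screening value as a prespecified covariate. Patients who die before discharge are placed in the worst category of each scale (beyond the highest NIHSS, below the lowest GCS). Report the adjusted effect with its 95% interval. Say also that the chi-square test of proportions is not the analysis for these two scores.

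The cost is a few sentences of analysis wording. Both scales are already recorded at screening and discharge, so no patients, visits or procedures are added. If a fuller analysis plan already specifies this, it is enough to align the two documents.

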### Determination of the sample size

The sample size was set at 500 to provide at least 80% power to detect a 6% absolute risk reduction in the primary outcome for patients in the individualized BP-lowering group compared to those in the guideline-recommended control group, using a two-sided significance test with 5% type I error. The following assumptions were made: a primary outcome of 60% in the control group will be reduced to 54% in the individualized group; and there will be 10% non-adherence to the treatment protocol and 5% overall loss to follow-up. The 60% incidence of unfavorable 90-day outcome is extrapolated from one Chinese study on severe stroke (NIHSS > 10) in 2013 [17]. The 10% non-adherence rate and the absolute risk reduction in primary outcome are extrapolated from the INTERACT1&2 studies which were designed to compare the effects of two different BP-lowering strategies in acute stroke patients [8, 18].

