## Background

Elevated blood pressure (BP) is one of the most common clinical manifestations in acute stroke; 70–84% [1–3] of stroke patients have a systolic blood pressure (SBP) > 140 mmHg on admission. Despite efforts by a few multicenter studies, the optimum management of BP in acute stroke is still an ongoing dilemma. The ACCESS study and CHHIPS study indicated that modest BP reduction brought down the mortality and the number of vascular events [4], whereas the SCAST study suggested that a careful BP-lowering treatment was associated with a higher risk of poor outcome. The results from the COSSACS study, CATIS study, ATACH-2 study, and INTERACT2 study are neutral: intensive lowering of BP did not reduce the mortality or severe disability significantly [5–8].

However, none of the above studies were targeted at patients with severe stroke. Acute severe strokes account for 13–24% of all strokes [9, 10] and are associated with cerebral hernia, acute cardiac failure [11], systemic complications [12], and death. Given the paucity, we initiated a multicenter randomized controlled trial (RCT) called CHASE, dedicated to test whether individualized antihypertensive treatment would lower the mortality and major disability in patients with severe stroke.

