### Randomization

A secure website (http://traillogin.applinzi.com) will be used to perform the centralized randomization (computerized random numbers). Patients will be randomized into one of the two intervention arms (1:1).

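### The stated power of at least 80% does not follow from the protocol's own inputs: 500 patients give about 26–27% power for 60% versus 54%, and less if non-adherence dilutes the effect

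*Protocol article*

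**What the plan says.** Under Determination of the sample size, the protocol article states: "The sample size was set at 500 to provide at least 80% power to detect a 6% absolute risk reduction in the primary outcome", comparing the individualized arm with the guideline arm "using a two-sided significance test with 5% type I error". The event rates are given as "a primary outcome of 60% in the control group will be reduced to 54% in the individualized group". Two allowances are listed: "there will be 10% non-adherence to the treatment protocol and 5% overall loss to follow-up".

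Other sections fix the remaining inputs. The Abstract (Methods/design) shows that 500 is the total and not the number per arm: "A total of 500 adult patients with acute severe stroke will be enrolled in 18 study sites in China". The Randomization section gives 1:1 allocation. The Statistical and analytical plan compares the proportions with a Chi-square test, analyses by intention to treat and calls two-sided p values of 0.05 or below significant.

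**The concern.** A fall from 60% to 54% is a small difference near the middle of the probability scale, where the binomial variance is close to its maximum. A two-arm trial of 500 looks far too small for it. Every input needed for the check is printed in the article, so this concerns a specific figure that is stated, not a detail left to another document.

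The power figure is the justification given for the sample size, and readers will use it to interpret the result. If the trial is believed to have 80% power for a 6-point benefit, a non-significant p value looks like fair evidence against that benefit. If the true power is about one in four, a real 6-point benefit would be missed about three times in four, and the same p value carries much less weight.

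**Working it through.** **Inputs** (protocol article)
- Control 60%, individualized 54%, two-sided 5%, power 80%, 10% non-adherence, 5% loss: Determination of the sample size.
- Total 500: Abstract. Allocation 1:1: Randomization. So 250 per arm, or 237.5 per arm after 5% loss (475 in all).
- Chi-square test, intention to treat: Statistical and analytical plan.

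**Formulas** (normal approximation to the Chi-square test, n per arm, mean proportion p̄ = (p1 + p2)/2)
- SE0 = √[2p̄(1 − p̄)/n]; SE1 = √[(p1(1 − p1) + p2(1 − p2))/n]
- Power = Φ[(p1 − p2 − 1.96·SE0)/SE1]
- n for 80% power = {1.96·√[2p̄(1 − p̄)] + 0.8416·√[p1(1 − p1) + p2(1 − p2)]}² / (p1 − p2)²

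**Step 1. Attempt to reproduce the stated 80%.** With n = 250 and p̄ = 0.57: SE0 = √(2 × 0.57 × 0.43/250) = 0.0443; SE1 = √[(0.2400 + 0.2484)/250] = 0.0442. Power = Φ[(0.06 − 1.96 × 0.0443)/0.0442] = Φ(−0.606) = 27.2%. The stated figure is not reproduced.

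**Step 2. Apply the 5% loss.** With n = 237.5: SE0 = 0.0454, SE1 = 0.0453, power = Φ(−0.640) = 26.1%.

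**Step 3. Apply the 10% non-adherence.** The article does not say how it was applied, so each case below is an assumption, on top of 5% loss.

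| Assumption | Proportions compared | n per arm | Power |
|---|---|---|---|
| Non-adherent patients removed (237.5 × 0.9) | 60% vs 54% | 213.75 | 23.9% |
| One-arm dilution, 6 × 0.9 = 5.4 points | 60% vs 54.6% | 237.5 | 22.0% |
| 10% crossover in both arms, 6 × 0.8 = 4.8 points | 59.4% vs 54.6% | 237.5 | 18.3% |

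**Step 4. Sample size that the inputs require.** n = (1.3723 + 0.5882)²/0.06² = 1,067.6, so 1,068 per arm and 2,136 in total. With 5% loss: 2,136/0.95 = 2,249. One-arm dilution would raise it further, to 1,316 per arm, or 2,632/0.95 = 2,771, but that rests on the Step 3 assumption.

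**Step 5. Other readings of the stated figure.**
- One-sided 5%, 250 per arm: 38.6%.
- 500 per arm (contradicted by the Abstract): 48.3% two-sided, 60.7% one-sided.
- With continuity correction, two-sided: 24.3% at 250 per arm, 23.2% after loss.

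None of these reaches 80%.

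**Step 6. What 500 patients can detect.** Starting from 60%, 80% power is reached at a difference of about 12.5 points with 250 per arm and about 12.8 points with 237.5 per arm. As a check, 60% versus 47% gives 83.2% and 81.3%.

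**Step 7. Precision.** The 95% half-width for the risk difference is 1.96 × √[(0.2400 + 0.2484)/n] = 8.7 points at n = 250 and 8.9 points at n = 237.5. At 475 evaluable, the interval excludes a 6-point benefit only when the estimate favours the guideline arm by more than about 8.9 − 6 = 2.9 points.

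**The case against.** The strongest defence is that the Abstract also announces a logistic model adjusted for site, demographics and baseline characteristics, and strong predictors can raise power above that of a crude Chi-square test. The principle is sound but the gain is too small. To match 2,136 patients with 475, adjustment would have to remove about 1 − 475/2,136 = 78% of the outcome variance. An assumed 30% reduction gives only about 35% power. The sample size section claims no such gain.

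It is also fair to say that the article cannot show which of its figures was mis-stated: the number of patients, the difference or the power. That stands, and the remedy should be reconciliation.

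A reader might infer more than the documents support:
- *That a null result would say almost nothing.* An interval of about ±9 points around an estimate near zero speaks against differences well above 9 points in either direction.
- *That the interval of a null result must contain the planned benefit.* It would not if the estimate leaned more than about 2.9 points towards harm.
- *That power is exactly 22%, or that 2,771 patients are needed.* Both depend on an unstated model of non-adherence.
- *That the 6-point reduction is itself an error*, because it is extrapolated from earlier blood-pressure trials and the Background says of a group of trials that "intensive lowering of BP did not reduce the mortality or severe disability significantly". A non-significant trial can still supply an effect estimate, and whether 6 points is a fair extrapolation depends on sources not at hand.

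**Conclusion.** The claim of "at least 80% power" is wrong on the article's own inputs. The firm figures are about 27% power with all 500 analysed and 26% after the stated loss, against a requirement of 2,136 patients before losses and about 2,250 with them. The planned number is therefore less than a quarter of what the stated design needs (500/2,136 = 23%). The lower figures of about 18–24% depend on how non-adherence acts. Uncertainty on that point moves the result by a few percentage points and does not affect the conclusion.

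The results rest on the normal approximation, equal arms and the unadjusted comparison. The consequence for interpretation is real but bounded: a non-significant result would often leave the planned benefit open, while still arguing against much larger effects.

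**What to change.** Reconcile the sample size, the difference and the power under Determination of the sample size. Re-deriving the number of patients from 60% versus 54% is one route. Since the Trial status section says recruitment has started, restating the power for 500 is the practical one:

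- State that 500 patients (about 475 evaluable) give roughly 22–27% power for 60% versus 54%, and say how non-adherence was modelled.
- State that 80% power is available only for a difference of about 12.5–13 points (60% to about 47%).
- Report the absolute risk difference with its 95% confidence interval, and say that non-significance will not be read as evidence of no effect. The absolute risk reduction is already planned, so only its interval is added.

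An ordinal analysis of the day-90 mRS could be added from data already collected. It is optional: its gain depends on an outcome distribution that the article does not give, and it does not correct the error.

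**Cost.** No extra patients or data are needed. The stated power becomes much less favourable. The change needs a protocol amendment, which under Protocol amendments requires agreement of the study group, sponsor and funder and then ethical approval.
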